### Data collection and quality management

A series of quality assurance methods has been established and will be applied before and during ESAR project. All relevant personnel, including clinicians, laboratory personnel, and project management personnel will receive unified training on theoretical perspective and practical procedure.

On enrollment, clinicians are required to be familiar with the inclusion and exclusion criteria. Every case needs to be included continuously without selection or omission, and will be reviewed by the project leader from Huashan Hospital before official enrollment. On data collection, clinicians will be trained with filling case report form (CRF) before official enrollment. Questions in CRF should be filled face-to-face by clinicians during enrollment and should not be hinted, induced or recalled afterwards. All relevant forms should be properly kept in a suitable place by a designated person to prevent burning, tearing, smearing, etc.

To ensure that each center conducts research in strict accordance with the plan, and the data is authentic and credible, quality control is carried out by the research team of Huashan Hospital Affiliated to Fudan University every six months. Supervisors will be assigned by the Huashan Hospital affiliated to Fudan University.

### Adverse event management

Potential adverse events and their management will be evaluated during follow up. In this study, 8ml peripheral blood and respiratory tract samples will be collected along with the routine clinical examination, which will not cause additional operations, burdens and costs to the subjects. Potential adverse events include localized pain, bruising or needle infections.

If a patient has any psychological discomfort in the process, the clinician should provide timely comfort and notify the relevant personnel to evaluate and record within 2 h. If ineffective, a psychologist will be arranged to conduct psychological assessment and consultation within 12 h, which will be recorded by designated personnel. The subjects can receive corresponding compensation and treatment when an unexpected injury or loss related to the research come out. Any adverse events in this study will be recorded in detail by a dedicated person. Clinicians must carefully inquire and trace any adverse events during the trial, strictly record them in the CRF, and finally report them to the ethics committee and relevant departments.

### Assessment and analysis of outcomes

The primary and secondary outcomes will be compared between group I and group II. Primary outcomes are time to start targeted antibiotic therapy. Secondary outcomes include incidence of clinically significant events (oxygen inhalation, ICU admission, tracheal intubation, tracheostomy, death, etc.), clinical remission rate (Meet all the following criteria for at least 24 h: (1) Heart rate < 100 bpm; (2) Blood pressure > 90 mmHg; (3) Body temperature < 38 °C; (4) Respiratory rate < 24/min; (5) Oxygen saturation at room temperature > 90%), hospitalization length within 28-day follow up.

SPSS 20 and Prism 8.0 will be applied for statistical analysis. Firstly, whether the enrolled cases met inclusion and exclusion criteria, and whether the actual number of enrolled, excluded, and dropped cases in each center are counted will be reviewed at the end of the study. Second, demographics characteristics, baseline information, follow-up status and outcomes will be compared between two groups. Statistical methods including *t* test or Mann–Whitney test, Pearson's chi-square test or Fisher test, cox method, Kaplan-Meier survival curve, log-rank method, logistic regression models will be applied in the form of two-tailed test. *P* < 0.05 was considered statistically significant.

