## Methods

### Study design

The study is a multicenter, open-label, randomized controlled, non-inferiority clinical trial recruiting patients with respiratory tract infections who meet inclusion and exclusion criteria (Table 1). Enrolled patients were divided into two groups in a 1:1 ratio [15]: Group I will be detected by mNGS for pathogens. Group II will first receive respiratory multiplex PCR, then mNGS in severe pneumonia (Table 2) if multiplex PCR results are negative or inconsistent with the clinical conditions. Disease condition and treatment status will be followed up every 7 days until reaching predefined outcomes within 28 days. If a participant with mild symptoms become severe during follow-up, respiratory samples should be collected again for mNGS detection. The detailed research process is shown in Fig. 1.

**Table 1 Tab1:** Inclusion and exclusion criteria

Inclusion criteria	• Aged from 18 to 80 years old • Unlimited gender • Newly developed cough, expectoration, purulent sputum, or exacerbation of original respiratory diseases within 14 days • Meet at least one of the following items: (1) Fever (> 38 ℃) (2) Consolidation signs and/or wet rales on chest physical examination (3) Leucocyte > 10*10^9^/l or < 4*10^9^/l (4) Patchy infiltration or interstitial changes on chest radiology
Exclusion criteria	• Highly-suspected of or confirmed with noninfectious lung diseases (tumor, autoimmune diseases, etc.) • The pathogen has been identified • Insufficient respiratory tract or blood specimen • Unable or refusing to cooperate due to physical or psychological factors • Participating in other clinical studies • Investigators or clinicians considers unsafe for the subject to participate
Exit criteria	• Participants request to withdraw from the interview

**Table 2 Tab2:** ATS/IDSA criteria for severe CAP

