### Sample size calculation

PASS 11 software was applied to calculate the sample size. Assuming hazard ratio (HR) = 1.50, *α* = 0.05, *β* = 0.10, and a 10% rate of participants in Group II receiving mNGS additionally, each group requires 200 subjects. Considering a 10% rate of lost to follow-up, each group needs 200 × 1.1 = 220 subjects; therefore, the total sample size of the two groups combined is calculated to be 440 subjects.

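### The trial is declared non-inferiority, but the only criterion stated is a two-tailed P < 0.05 difference test, and no margin, direction or test group is identified

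*Protocol article*

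**What the plan says.** **Design.** Study design states: "The study is a multicenter, open-label, randomized controlled, non-inferiority clinical trial recruiting patients with respiratory tract infections". The Methods paragraph of the abstract uses the same label.

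**Primary endpoint.** Assessment and analysis of outcomes: "Primary outcomes are time to start targeted antibiotic therapy". This is a time to event, and the event is a favourable one.

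**Comparison and criterion.** The same section says: "The primary and secondary outcomes will be compared between group I and group II". It then lists t, Mann–Whitney, chi-square, Fisher, Cox, Kaplan–Meier, log-rank and logistic methods, which "will be applied in the form of two-tailed test". The threshold is P "< 0.05 was considered statistically significant".

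**Sample size.** Sample size calculation begins "Assuming hazard ratio (HR) = 1.50", with α = 0.05, β = 0.10 and "a 10% rate of participants in Group II receiving mNGS additionally, each group requires 200 subjects". A 10% allowance for loss to follow-up brings this to 220 per group and 440 in total. The section gives no sidedness for α, no orientation for the HR and no expected proportion of patients with the event.

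No section states a margin, non-inferiority hypotheses, a confidence-limit rule, or which strategy is to be shown non-inferior to the other.

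**The concern.** A non-inferiority trial has to exclude a deficit larger than a stated margin. A two-tailed test at P < 0.05 asks whether the groups differ at all, which is a different question, and its answer can point the other way. The design label and the stated criterion therefore do not fit together.

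The HR of 1.50 does not close the gap. It is introduced as an assumption and could be either an expected benefit or a margin. Its direction also matters. Because starting targeted treatment is favourable, a slower Group II has an HR (II vs I) below 1. A margin of 1.50 must then act as a lower bound of 0.667 on that ratio or, equivalently, as an upper bound of 1.50 on the ratio I vs II.

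At stake is the primary conclusion. In an open-label trial, a margin, direction or design type settled after results are known would not support a non-inferiority claim.

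**Working it through.** **1. The plan's own figure.** Inputs from Sample size calculation: HR 1.50, α 0.05, power 0.90. By Schoenfeld's formula, two-sided with 1:1 allocation:

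events = 4 × (1.960 + 1.2816)² / (ln 1.5)² = 255.7, so 256.

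One-sided at 0.05 gives 209. Allowing for the 10% of Group II who also receive mNGS, under several common methods and both the Schoenfeld and Freedman formulas, gives 282–325 events two-sided or 230–266 one-sided. None of these equals 400. With no event proportion stated, 200 per group can be neither reproduced nor refuted. The last steps are arithmetically right: 200 × 1.1 = 220, and 2 × 220 = 440.

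**2. Does the sample size show which design was meant?** Non-inferiority with margin ratio 1.50, true HR 1 and one-sided α 0.025 needs 4 × (1.960 + 1.2816)² / (ln 1.5 − ln 1)² = 256 events. This is the same number as superiority at HR 1.50 with two-sided α 0.05, so the calculation does not tell them apart.

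**3. The two criteria can disagree.** With SE(log HR) = 2/√D for D events, and 0.667 as an illustrative bound:

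- D = 400: SE = 0.100 and the 95% CI factor is exp(1.96 × 0.100) = 1.217. An observed HR (II vs I) of 0.82 has limits 0.82/1.217 = 0.674 and 0.82 × 1.217 = 0.998. It is significantly worse, yet within the margin.
- D = 256: SE = 0.125 and the factor is exp(1.96 × 0.125) = 1.278. An observed HR of 0.80 has limits 0.80/1.278 = 0.626 and 0.80 × 1.278 = 1.022. It is not significant, yet the margin is not excluded.

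**4. If non-significance were read as non-inferiority.** P(|Z| < 1.96), where Z has mean |ln HR|/SE and variance 1. Event counts are assumptions.

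| True HR | Events | Mean of Z | P ≥ 0.05 |
|---|---|---|---|
| 0.667 (II vs I) | 256 | 0.4055/0.1250 = 3.24 | 10% |
| 0.667 (II vs I) | 320 | 0.4055/0.1118 = 3.63 | 5% |
| 0.667 (II vs I) | 400 | 0.4055/0.1000 = 4.05 | 2% |
| 1.2 against one strategy | 240 | 0.1823/0.1291 = 1.41 | 71% |
| 1.2 against one strategy | 320 | 0.1823/0.1118 = 1.63 | 63% |
| 1.2 against one strategy | 400 | 0.1823/0.1000 = 1.82 | 55% |

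A rule requiring the lower 95% limit to exceed 0.667 passes a true HR of 0.667 in 2.5% of trials, whatever the event count.

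**5. What the planned size supports under a confidence-limit rule.** One-sided α 0.025, true HR 1. Events for 90% power = 4 × (1.960 + 1.2816)² / (ln margin)². Power with D events = Φ(√D/2 × ln margin − 1.96). The margins are assumptions.

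| Margin ratio | Events for 90% power | Power, 400 events | Power, 320 events |
|---|---|---|---|
| 1.50 | 256 | 98% | 95% |
| 1.33 | 517 | 81% | 72% |
| 1.25 | 845 | 61% | 51% |

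Each patient contributes at most one event, so 517 and 845 exceed the 440 patients planned.

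**The case against.** The strongest reply is that this is a condensed article. The sentence on tests is a general methods list that also covers baseline data and secondary outcomes, and margins and analysis sets often sit in a full protocol or SAP. The list includes a Cox model, whose two-sided 95% interval matches the two-tailed 0.05 level and is a standard non-inferiority tool. The 1.50 can be read coherently as an upper bound on the ratio I vs II. The Discussion, which sets PCR combined with mNGS against direct mNGS, suggests that Group II is the strategy under test.

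Much of this stands, and it rules out two stronger readings. A reader might infer that P ≥ 0.05 is the trial's only route to a non-inferiority claim. No section says a non-significant result will be read that way. A reader might also infer that a truly equivalent strategy has no valid route to success. The Cox interval offers one, although the article does not spell it out.

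Nor are the percentages in step 4 this trial's expected error rates. At a true HR of 0.667, the rate falls to 2.5% once ln(1.5) × √D/2 = 1.96 + 1.96, that is at D = 4 × 3.92²/0.4055² ≈ 374 events, a count that 400 evaluable patients could reach.

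The mismatch itself survives. The article does not merely leave a criterion out. It states one, and that criterion belongs to a different design. The reading of 1.50 as a margin has to be supplied by the reader.

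**Conclusion.** The point holds as a contradiction between the declared design and the stated criterion. As written, the plan cannot answer a non-inferiority question: its criterion tests for a difference, its HR of 1.50 is neither identified as a margin nor oriented, and the group under test is not named.

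The consequence is conditional. Only if non-significance were taken as non-inferiority would the step 4 rates apply: 10% to 2% for a true HR of 0.667 with 256 to 400 events, and 71% to 55% for a true HR of 1.2 against one strategy with 240 to 400 events. These assume proportional hazards, equal allocation and the event counts shown.

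The documents do not show the sample size to be wrong. It is adequate for a margin of 1.50 if about 256 of the 400 evaluable patients (64%) start targeted treatment and the true HR is 1. It falls short of 90% power for margins of 1.33 or tighter.

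**What to change.** In Assessment and analysis of outcomes, replace the P < 0.05 criterion for the primary endpoint with a rule such as:

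> Group II (multiplex PCR, then mNGS where indicated) is non-inferior to Group I (direct mNGS) if the lower limit of the two-sided 95% confidence interval for the Cox hazard ratio of starting targeted treatment (II vs I, a higher ratio meaning an earlier start) exceeds [margin]. A P value of 0.05 or more is not evidence of non-inferiority.

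The sponsor should confirm that Group II is the strategy under test, state and justify the margin, and give the sidedness of α and the assumed event proportion in Sample size calculation.

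The cost depends on what 1.50 was meant to be:

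- **The margin, confirmed and justified.** The bound is 1/1.50 = 0.667. The change is wording only, provided about 256 events are expected.
- **A stricter margin is needed.** The planned 440 patients do not give 90% power at 1.33 or 1.25. The stated power would have to be restated or the trial enlarged.
- **An expected benefit.** Delete the non-inferiority label from the abstract and Study design and present a superiority trial. The two-tailed test then fits, and the change is wording only.

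The choice should be fixed and dated before any comparison of outcomes by group.

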### Confidentiality

Participants’ personal information is strictly restricted to outcome evaluation of study regimen. Paper documents containing participants information will be saved in a dedicated office in cooperative hospitals. Digital documents will be kept in password-protected files on website. The study documents can only be accessed by authorized personnel.

## Discussion

Exploring the efficiency of different diagnosis strategies is of great significance for optimizing ARI early management and prognosis. Since multiplex PCR was first applied by Chamberlian et al. to screen missing locus on Duchenne muscular dystrophy in 1988 [17], it has been successfully applied in many fields. The sensitivity and specificity of respiratory multiplex PCR has been proved to be higher than 90% [18]. Shengchen et al. [19] reported that FA-RP can shorten the length of stay and reduce antibiotic administration in hospitalized adults with lower respiratory tract infection. Similarly, our previous study [20] found that 53.8% received antiviral therapy and 69.6% received antibiotics adjustment in multiplex PCR group, while 12.7% and 5.1% in traditional examination group, indicating a positive effect on outcomes. Simultaneously, FA-RP can also lower the risk of infectious disease transmission [20]. However, Brendish et al. [21] argued that multiplex PCR was not associated with a reduction in the overall duration of antibiotic use in hospitalized adults with acute respiratory illness. Besides, multiplex PCR cannot detect rare or unknown respiratory pathogens.

Compared with traditional culture, mNGS improves sensitivity and shortens time to identify various pathogens [22]. The sensitivity and specificity in BALF samples were 88.89% and 14.86% [23], and 34% of candidate pathogens can be detected by mNGS [24] to provide more accurate diagnostic information. Furthermore, it can screen rare pathogens [25] such as COVID-19 [26] and Nocardia [27], but subject to missing detection, expensive equipment and high personnel demand. There is few studied reporting impact of mNGS on ARI prognosis. Zhang et al. [28] performed repeated mNGS testing in nine patients with suspected central nervous system infection (CNS) and found that mNGS semi-quantitative values can be used to dynamically monitor pathogen load and disease progression. Hongxia Duan et al. [29] suggested that 28-day mortality in mNGS-positive group was higher (9.0% vs 0%, *P *= 0.049), but the average survival time (176.64 vs 150.96 days, *P *= 0.425) was not statistically different, indicating that positive results were correlated with worse prognosis. However, these studies did not analyze the influence of antibiotics, which might lead to the lower detection rate by traditional methods.

Although mNGS can cover most pathogens, it requires longer time than respiratory multiplex PCR. Moreover, the expensive cost makes mNGS not a panacea for any respiratory infection, but a technology that can be used in specific situations. Therefore, based on previous research, ESAR is designed to compare a combination of respiratory multiplex PCR and mNGS with direct mNGS detection to optimize diagnosis pathway in ARI.

This study has several limitations. Firstly, although multiplex PCR and mNGS will be performed in the central laboratory, there existed certain heterogeneity for traditional respiratory specimen detection method between hospitals. In addition, all the methods above still cannot directly distinguish pathogenic organism and colonization. The reports will be interpreted by experienced clinicians and controversial cases will be discussed and diagnosed by experts.

## Data Availability

Not applicable.

## Abbreviations

WHO: World Health Organization
LRTI: Lower respiratory tract infection
qPCR: Real-time quantitative PCR
RT-PCR: Reverse transcription PCR
dPCR: Digital PCR
ddPCR: Digital droplet PCR
FA-RP: Filmarray respiratory detection system
NPS: Nasopharyngeal swab
TB: Tuberculosis
MTB: Mycobacterium tuberculosis
RIF: Rifampicin
POCT: Real-time checkout
ARIs: Acute respiratory infections
mNGS: Next generation metagenomic sequencing
PCR: Polymerase chain reaction
CRF: Case report form
COVID-19: Novel coronavirus pneumonia
H1N1: Swine-origin influenza A virus
BALF: Bronchoalveolar fluid
HR: Hazard ratio
CNS: Nervous system infection
